## Abstract

**Background:**

Subjective tinnitus is a phantom sensation experienced in the absence of any source of sound. Its mechanism remains unclear, and no approved drugs are available. Vagus nerve stimulation (VNS) is an exciting new method to treat tinnitus, but direct electrical stimulation of the cervical vagus has disadvantages. This randomized controlled clinical trial aims to overcome these limitations by stimulating the auricular branch of vagus nerve (ABVN) on the outer ear. Since the ABVN is the only peripheral branch of the vagus nerve distributed on the ear’s surface, it should be possible to achieve analogous efficacy to VNS by activating the central vagal pathways. However, researches have indicated that the curative effect lies in a combination of auditory and vagal nerve stimulation. Moreover, from traditional Chinese theory, auricular acupoints used to treat tinnitus are mainly in the regions supplied by the ABVN. Whether stimulation at the auricular acupoints is due to unintentional stimulation of vagal afferent fibers also needs evidence.

**Methods/design:**

A total of 120 subjects with subjective tinnitus are randomized equally into four groups: (1) electrical stimulation at auricular acupoints (CO10, CO11, CO12, and TF4) innervated by the ABVN; (2) electrical stimulation at auricular acupoints (CO10, CO11, CO12, and TF4) innervated by ABVN pairing tones; (3) electrical stimulation at auricular acupoints innervated by non-ABVN pairing tones; (4) electrical acupuncture. Patients will be treated for 30 minutes every other day for 8 weeks. The primary outcome measure is the Tinnitus Handicap Inventory. The secondary outcome measure combines a visual analogue scale to measure tinnitus disturbance and loudness with the Hospital Anxiety and Depression Scale. Assessment is planned at baseline (before treatment) and in the 4th and 8th week, with further follow-up visits after termination of the treatment at the 12th week. Any adverse events will be promptly documented.

**Discussion:**

Completion of this trial will help to confirm whether ABVN or the combination of ABVN and sound stimulus plays a more important role in treating tinnitus. Moreover, the result of this clinical trial will enhance our understanding of specific auricular acupoints.

**Trial registration:**

Chinese Clinical Trials Register ChiCTR-TRC-14004940.

## Background

Subjective tinnitus is considered as a phantom sensation experienced in the absence of any internal or external acoustic stimulus. It can be perceived as a hissing, buzzing, humming, roaring, whistling, or ringing sound in one or both ears, or somewhere in the head. At present, tinnitus has becoming the most common otology problem, affecting 10% to 30% of the general population and an estimated prevalence of 24.2% in the older population [1]. Meanwhile, with the growing popularity of electronic music, young people experience transient or permanent tinnitus at a ratio of 89.5% and 14.8%, respectively, after exposure to loud music [2]. Among severe tinnitus sufferers, tinnitus-related sensations, such as anxiety, annoyance, frustration, and depression lead to a negative impact on quality of life in 70% of those affected [3], and they are usually told that they must learn to live with it. Yet the pathological mechanisms that underlie tinnitus perception remain largely hypothetical and are still not well understood. Currently, the universally accepted hypothesis is that interactions between altered cochlear inputs and distorted central auditory processing provoke tinnitus. Studies have supported that subjective tinnitus may be a result of the expression of neural plasticity and that anomalies may develop because of decreased input from the ear, deprivation and sound stimulation, overstimulation or other factors as yet unknown. For the buried pathological mechanisms, treatment options are limited. No physiotherapy treatments can yet be considered sufficient in providing long-term reduction of tinnitus impact and there is no drug approved by the European Medicines Agency or the Food and Drug Administration on the market [4,5]. Therefore, an effective and safe therapy for tinnitus is of considerable importance to meet this significant unmet clinical need.

Vagus nerve stimulation (VNS) is approved by the Food and Drug Administration for both refractory epilepsy and resistant depression [6,7]. VNS offers an exciting new perspective for the treatment of tinnitus and it has recently been demonstrated that VNS is a promising method [8]. In this method, an electrode surgically implanted around the left cervical vagus nerve is connected to a pulse generator placed subcutaneously in the upper chest. However, considering the disadvantages of the implantation, including lesions of the vagus nerve, infection, shortness of breath, possible mechanical failure of electronic equipment, and battery replacement, a relatively safe and well tolerated improved method is desired. To minimize side effects, stimulation of the auricular branch of vagus nerve (ABVN) has been suggested [9]. The ABVN is the only peripheral branch of the vagus nerve distributed on the surface of ear, and studies using the transganglionic horseradish peroxidase method [10,11] have shown that it mainly projects to the nucleus of the solitary tract in the brainstem. Functional magnetic resonance imaging and vagus sensory evoked potentials revealed that ABVN stimulation shows considerable similarity to implanted VNS, with both acting through the central auditory pathway of the vagus nerve [12,13]. Thus, it would be safer simply to deliver mild electric shocks to the skin of the outer ear instead of resorting to VNS with surgery. However, some researchers reported that ABVN stimulation alone seems to have no relevant improvement of tinnitus complaints [8,14], and it is suggested that the combination with other interventions, such as sound stimuli, which would reduce the cortical response to mid-frequency tones, increase frequency selectivity, and decrease cortical synchronization [15] should be considered. But there is not currently enough evidence in clinical practice of the effect of the method of pairing tones with stimulation at ABVN.

Moreover, auricular acupuncture, the underlying mechanism of which is unclear, has been used to treat tinnitus for thousands of years [16]. Auricular acupoints applied to treat tinnitus such as Kidney (CO10), Yidan (CO11), Liver (CO12) and Shenmen (TF4) are distributed in the regions supplied by ABVN [17]. So whether auricular acupoints are due to an unintentional stimulation of the vagal afferent fibers also needs more clinical and experimental evidence.

Therefore, we have designed a randomized, four-arm, controlled clinical study to provide a conclusive answer. In this trial, our aim is to attempt to confirm whether ABVN or the combination of ABVN and sound stimulus plays a more important role in the treatment of tinnitus. Moreover, the result of this clinical trial will enhance our understanding of specific auricular acupoints.

## Methods/design

### Design

This is a randomized, single-blind, four-armed, controlled clinical trial conducted in Yichang Hospital of Traditional Chinese Medicine, Clinical Medical College of Traditional Chinese Medicine, China Three Gorges University. Study patients will be screened based on specific inclusion and exclusion criteria. Before beginning the treatment, all candidates will undergo a standard neuro-otological examination and a baseline audiometric assessment, including measurement of hearing thresholds, minimal masking levels, loudness discomfort levels, and stapedial reflexes, performed by professional audiologists. Then they will be equally randomized into four groups: (1) electrical stimulation at auricular acupoints (CO10, CO11, CO12, and TF4) innervated by ABVN (the ABVN group); (2) electrical stimulation at auricular acupoints (CO10, CO11, CO12, and TF4) innervated by ABVN pairing tones (the ABVN plus tone group); (3) electrical stimulation at auricular acupoints innervated by non-ABVN pairing tones (the non-ABVN plus tone group); (4) an electrical acupuncture group. Detailed information regarding the clinical procedures is presented in Figure 1. The clinical endpoints are assessed by blinded independent statisticians. Any adverse effects during the course will be reported. This trial was registered on the Chinese Clinical Trial Register (ChiCTR-TRC-14004940).

**Figure 1 Fig1:**
[figure not shown]
**Flow chart.** ABVN, auricular branch of vagus nerve; HADS, Hospital Anxiety and Depression Scale; THI, Tinnitus Handicap Inventory; VAS, visual analogue scale.

The trial will be performed according to the principles of the Declaration of Helsinki (Edinburgh version, 2000). In addition, written informed consent will be obtained from all participants. Ethical permission was obtained from the Research Ethical Committee of Yichang Hospital of Traditional Chinese Medicine, Clinical Medical College of Traditional Chinese Medicine, China Three Gorges University. The ethics committee approval number is 201407041.

### Recruitment period and methods

Patients will be enrolled in Yichang Hospital of Traditional Chinese Medicine, Clinical Medical College of Traditional Chinese Medicine, China Three Gorges University with a target sample size of 120 subjects. We will recruit the participants by advertising in the hospitals, in public newspapers and on the internet homepages of hospitals. The trial will be executed from July 2014 to July 2015.

### Types of participant

#### Inclusion criteria

Qualified participants meeting all of the following conditions will be recruited [18,19]:Single-tone subjective tinnitus, typical conditions of unilateral or bilateral;Age 15 to 65 years, either sex;Recurrent attacks for more than 1 month or persist attacks for more than 5 days;Must be able to hear stimulation tones presented by the device at all frequencies;Must be able to complete the forms and use the rating scales;Not be taking part in any other clinical trial during the period;Voluntarily signed informed consent forms.

#### Exclusion criteria

Participants who experience or have one or more of the following conditions will be excluded:Objective tinnitus or Ménière’s disease;Tinnitus induced by otitis media, otitis interna or cerebellopontine angle tumors;Postcochlear lesion;Patients with severe diabetes, hypertension or cardiovascular disease, or mental disease;Patients unable to read, understand and complete the forms or use the rating scales;Pregnant or preparing for pregnancy.

### Randomization and blinding

One researcher screens and enrolls participants at the clinic. Patients are numbered according to registration order. After participants have completed a baseline evaluation, another researcher who is uninvolved with data collection randomly assigns them to one of four treatment groups in a 1:1:1:1 ratio using a computer-generated, blocked randomization sequence generated using SPSS 15.0 software (SPSS Inc., Chicago, IL, USA). This researcher informs the therapist of the treatment assignment.

We applied a single-blind design in which the study patients, data collocation staff, and data analysts are blinded during the study protocol. The therapists are not blinded to the treatments they deliver because treatment manipulation makes it impossible. During the intervention, therapists and data collection staff are instructed not to exchange information with each other nor communicate with the study patients.

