### ABVN group

All participants will receive transcutaneous electrical stimulation at auricular acupoints innervated by the ABVN. The points are located at the cymba conchae and the triangular fossa, where there is rich ABVN distribution [17]. Main stimulation points according to standard practice include Kidney (CO10), Yidan (CO11), Liver (CO12), and Shenmen (TF4). A transcutaneous electrical nerve stimulator (Suzhou Medical Appliance Co. Ltd., Suzhou, China) will be used in this group. Two carbon-impregnated silicone electrode tips are connected to the transcutaneous electrical nerve stimulator by metal wire; one tip contacts the skin surface points and the other acts as a terminal end in the ear. The stimulation frequency is 20 Hz, the stimulation current is 1 to 5 mA, with stimulus pulses shorter than 1 ms in duration. Each session will last 30 minutes; sessions are performed every other day for 8 weeks.

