### ABVN plus tone group

The format will be exactly the same as for the ABVN group. Multiple tones will be delivered by Tinnitus Measurer software (Neonix, USA) at a comfortable listening level during the transcutaneous electrical nerve stimulation. Randomly interleaved pure tones that span the hearing range but exclude the tinnitus tone will be selected. Each session will last 30 minutes; sessions are performed every other day for 8 weeks.

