### Electrical acupuncture group

The subjects of this group will be treated with electrical acupuncture at local and distal points. Acupuncture points are selected as follows. 1. local acupoints: Yifeng (TE17), Tinghui (GB2); 2. distal acupoints: Xiaxi (GB43), Zhongzhu (TE3). Patients will be in a comfortable and relaxed position and asked to concentrate on the treatment task. After the needles are inserted into the acupoints, they will be connected to an electrical point stimulation device (G6805-2A, Shanghai Huayi Medical Instrument CO., Ltd, Shanghai, China) operating at a frequency of 20 Hz and current of 1 to 5 mA, with pulses shorter than 1 ms in duration. The intensity will be adjusted individually based on the tolerance of the patient. All parameters of the electrical stimulation inducing twitching of the muscles indicate effective stimulus. After retaining the needles for 30 min, all needles are taken out using alcohol-soaked cotton balls to avoid infection and bleeding.

The needles (Suzhou Medical Supplies Factory Co., Ltd. Suzhou, China) used in this group are 25 mm in length and 0.3 mm in diameter. Electrical acupuncture is performed by a therapist with rich clinical experience and acupuncture licenses for Chinese medicine practitioners from the Ministry of Health of China. Treatment will be conducted over a period of 8 weeks, at a frequency of every other day.

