However, our study has several potential limitations. First, all the outcome measures are self-assessments instead of objective measures. To some extent, objective measures carry out relatively convincing evidence. However, the Tinnitus Handicap Inventory [55,56], visual analogue scale [56], and Hospital Anxiety and Depression Scale [57] have been much used in most of the randomized controlled trials on tinnitus and they are proved to be efficient in reflecting the subjective emotional changes related to tinnitus. Second, this trial is single-blind, therefore, the subjective factors from therapists might bias the outcome assessments. However, it is hard to blind the therapists, who are required to be familiar with treatments for the specific grouping assignment. Another limitation concerns the fact that this is a single center study. It does not lend results to great generalizability to more diverse sets of patients in more diverse regions. In addition, the sample size in this study is relatively small. A large sample, multicenter, and objective measures to assess the effectiveness of treatment should be included in a future study.

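### Patients are declared blinded, but in five of the six planned contrasts they can tell the treatments apart, and they score every outcome themselves

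*Protocol article*

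**What the plan says.** Under Randomization and blinding, the protocol article states that "the study patients, data collocation staff, and data analysts are blinded during the study protocol". The same section makes an exception for one party only: "The therapists are not blinded to the treatments they deliver because treatment manipulation makes it impossible". The Design section adds: "The clinical endpoints are assessed by blinded independent statisticians".

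The sections on the four arms describe what the patient experiences:

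- **ABVN:** "All participants will receive transcutaneous electrical stimulation at auricular acupoints innervated by the ABVN". No tones are mentioned.
- **ABVN plus tone:** the same electrical stimulation, and "Multiple tones will be delivered by Tinnitus Measurer software", "at a comfortable listening level during the transcutaneous electrical nerve stimulation".
- **Non-ABVN plus tone:** the same format as ABVN plus tone, but at ear points supplied by a different nerve.
- **Electrical acupuncture:** "After the needles are inserted into the acupoints, they will be connected to an electrical point stimulation device". Needles go in at local and distal points, and muscle twitching is the sign of an effective stimulus.

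In the limitations paragraph of the Discussion, the authors say that "all the outcome measures are self-assessments instead of objective measures". They then treat incomplete blinding as a matter of therapist influence only.

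**The concern.** Blinding of patients matters most when the patient is also the person who scores the outcome. That is so here for the Tinnitus Handicap Inventory (primary), the visual analogue scales and the Hospital Anxiety and Depression Scale. A patient who knows whether needles were used, or whether tones were played, can carry an expectation about that treatment into the questionnaire. Data staff and analysts who do not know the allocation cannot remove what is already in the score.

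The contrasts most exposed are the ones the plan puts first, each ear-stimulation arm against electrical acupuncture. ABVN alone against ABVN plus tone, which carries the trial's stated aim, is also exposed. As the text stands, a difference in any of these would be reported as coming from a patient-blinded comparison.

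**Working it through.** **Step 1. What a patient can perceive, by arm** (from the Interventions sections)

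| Arm | Needle or surface electrode | Tones heard |
|---|---|---|
| ABVN | surface, ear | no |
| ABVN plus tone | surface, ear | yes |
| Non-ABVN plus tone | surface, ear (other site) | yes |
| Electrical acupuncture | needle | no |

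The tones cannot be assumed to go unnoticed: the inclusion criteria require every participant to be able to hear them. The article describes no sham needle, dummy electrode or silent tone channel.

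**Step 2. The planned contrasts** (Statistical analysis section). Four arms give 4 × 3 / 2 = 6 pairs. Three are first-stage contrasts against electrical acupuncture. The other three, among the ear-stimulation arms, follow if a difference is found.

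| Contrast | Stage | Needle/electrode differs | Tones differ | Patient can tell them apart |
|---|---|---|---|---|
| ABVN plus tone vs electrical acupuncture | 1 | yes | yes | yes |
| Non-ABVN plus tone vs electrical acupuncture | 1 | yes | yes | yes |
| ABVN vs electrical acupuncture | 1 | yes | no | yes |
| ABVN vs ABVN plus tone | 2 | no | yes | yes |
| ABVN vs non-ABVN plus tone | 2 | no | yes | yes |
| ABVN plus tone vs non-ABVN plus tone | 2 | no | no | not by needle or tone; ear site differs |

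Count: 3 of 3 at the first stage plus 2 of 3 at the second stage gives 5 of 6.

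**Step 3. Who scores.** The outcome sections describe questionnaires and line scales that the patient completes, and the Discussion confirms that this holds for all outcomes. The patient is therefore the assessor. The Design section gives that role to statisticians. This fits their analysing the data, but not their scoring the endpoints.

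**Step 4. The plan's own figure.** The blinding claim rests on no number. The sample size does reproduce. With P1 = 0.28, P2 = 0.0097 and mean P = 0.14485, the stated formula gives (1.960 + 0.842)² × 2 × 0.14485 × 0.85515 / (0.2703)² = 26.6, so 27 per group. Then 27 / 0.90 = 30 per group and 120 in total. This point leaves those figures unchanged.

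**The case against.** **Open-label may say too much.** A reader might infer that five contrasts are simply open-label. The documents do not support that much. All four arms give real stimulation, and a patient who perceives the modality need not know the hypothesis, which arm is the comparator, or which is expected to do better. What patients are told belongs largely to consent material that is not shown. The authors may have meant this narrower masking. This stands as a limit on the label. It does not rescue the sentence, which claims patient blinding without qualification.

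**A size for the bias is tempting.** If expectation moved the Tinnitus Handicap Inventory by 4 to 6 points and the SD were 20, the shift would be 0.20 to 0.30 SD. Against the 0.78 SD detectable with 27 per group (t-test, 80% power, unadjusted 5%), that is 26% to 39%. Neither the shift nor the SD is in the protocol. At SD 15 the share is 34% to 51%, and at SD 25 it is 21% to 31%. With Bonferroni for three comparisons the detectable difference is about 0.91 SD, and the share at SD 20 is 22% to 33%. The direction is also unknown: expectation could favour a new device or a long-accepted needle treatment. These figures carry no weight in the conclusion.

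**Self-report is already admitted.** This is true. The limitations paragraph lists it first, but as a lack of objectivity. It does not connect it with patients knowing their treatment, so the gap is real but narrow.

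**The sentence about statisticians may be loose wording** for analysis. That is likely, and it needs rewording, not removal.

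**The differences are inherent in the comparison.** Needles, electrodes and tones cannot be made to feel alike simply by asking. This is also true, and full masking is not requested. It is a reason not to claim it.

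**Conclusion.** The statement that patients are blinded is wrong as written. By the article's own description, patients can distinguish the treatments in 5 of the 6 planned contrasts, including every first-stage contrast and ABVN versus ABVN plus tone. Because every outcome is self-assessed, the blinding of data staff and analysts does not protect these contrasts from expectation bias. How large that bias is, and which arm it favours, cannot be derived from the document.

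Patient masking is plausible in one contrast, ABVN plus tone against non-ABVN plus tone. It is not assured there, because the ear site differs and the ethics section notes rare reflexes specific to ABVN stimulation. This remains the contrast best placed to carry a vagus-specific conclusion.

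The verdict assumes that no masking exists beyond what the article describes. It does not assume that patients know the hypothesis.

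**What to change.** 1. **Randomization and blinding:** withdraw the general claim that patients are blinded. Say what they are kept unaware of, for example the hypothesis, if that is so. Limit any claim of patient masking to ABVN plus tone against non-ABVN plus tone, noting that the ear site differs.
2. **Design:** change *assessed by* to *analysed by* for the statisticians, and state that patients score the endpoints.
3. **Discussion, limitations:** name patient expectation as a limitation of the other five contrasts.
4. **Reporting:** describe those five contrasts as not patient-blinded, and rest any vagus-specific conclusion on ABVN plus tone against non-ABVN plus tone.

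The cost is a few sentences and a less favourable blinding claim. No arm, visit, sample size or treatment changes. The trial is still recruiting, so the wording can be corrected before results are known.

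A treatment-guess question at an existing visit is optional. Asked after treatment, it may reflect perceived benefit as much as unblinding. Changing what patients are told is not part of this fix; it would not reach those already enrolled and may need ethics review.
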